## Methods/design

This study has been approved by the Research Ethics Board of the Miguel Hernández University, and we obtained informed consent from each participant. Furthermore, participants signed a commitment of confidentiality regarding the content of the assigned treatment.

### Description of the overall project

The study consists of two phases, both based on the same population.

Phase I, conducted over the course of 1 year, is a cross-sectional study with two measurement stages and the following three aims:

1. We will seek to gain access to the reference population, identify the eligible population, select the study population and identify the prevalence of our selected walking criteria (stage 1). The results of stage 1 are included in this paper.

2. We will seek to identify the predictors of the behavioral intention to carry out the selected walking program using the TPB and exploring the role of pain, impact of FM and fear of movement (stage 2).

3. We will seek to explore the concordance of walking behavior measurements (subjective and objective measures) (stage 2).

Phase II, which will be conducted over the course of 2 years, is an experimental, randomized, triple-blind study with two treatment groups and one active control group. Longitudinal measures will be taken at baseline and at 7 weeks, 3 months and 9 months of postexperimental intervention. One group will receive a motivational plus implementation intentions intervention (MIG), a second group will receive only an implementation intention intervention (IG) and the control group (CG) will be given a neutral task related to postural hygiene. The three groups will receive the same information on the benefits of physical exercise in FM. Motivational intervention will be based on the predictors of behavioral intention as measured and identified in phase I (stage 2) in order to create or strengthen the behavioral intention during the experimental study.

This triple-blind study includes masking of the following groups in the manner described. Participants will know only that there are different intervention sessions but will not know the session contents; moreover, they will be unaware of the assumptions regarding the superiority of one intervention over another. Measures will be taken by researchers who do not participate in the treatment application and who are blinded to the experimental conditions. The statistician will also be blinded to the study protocol. The researchers who apply implementation intentions will also be blinded with respect to the MIG or IG experimental condition. In this phase, we aim to study the efficacy of the MIG intervention on unsupervised walking over the short term (7 weeks), medium term (3 months) and long term (9 months). The measurement at 7 weeks will be taken during the week after completion of the 6-week minimum walking program. We will base the selection of the medium- and long-term measurements on the assumption that the highest percentage of dropouts occurs between 3 and 6 months in supervised physical exercise programs
[8,9]. On the day of the intervention, a researcher will be responsible for the distribution of the participants into the three different treatment groups following random assignment. The researcher will remind participants of their confidentiality commitment.

Our main hypothesis is that a combined intervention (both motivational and volitional) will significantly increase walking behavior in comparison to the control group and that this effect will be higher than that in a merely volitional intervention in the short term and stable in the medium and long term.

Our selected walking pattern for FM patients is between two and four times weekly for about 50 minutes in bouts of 15 to 20 minutes, with a small rest between bouts to allow patients to avoid fatigue and continue the activity, for a minimum of six consecutive weeks
[31]. We chose this pattern because it includes several components which will encourage FM patients to do unsupervised physical exercise. Walking is an accessible, cheap and flexible activity; it includes resting; and it requires minimal time, which aids habit acquisition. Although we selected this pattern, we reduced the minimum daily time to 30 minutes (in two bouts of 15 minutes each) and at least two times weekly because our target population is sedentary. In addition, patients will be advised to start physical exercise gradually
[10,11], beginning with a low, comfortable intensity according to differences in physical capacity
[4]. It is well known that FM patients can benefit from low-intensity walking programs 2 or 3 days per week
[32]. Moreover, 30 minutes of continued physical activity has also been shown to have positive effects on health in the general population
[33].

### Study population and recruitment process

The fibromyalgia associations of Alicante (ADEFA), Elche (AFEFE), Madrid (AFIBROM) and Talavera de la Reina (AFIBROTAR) collectively comprise a total of 2,438 members with a clinical diagnosis of FM (75.8% diagnosed by rheumatologists, 9.2% by general practitioners, 5.3% by traumatologists, 2.2% by clinical rehabilitation specialists, 0.7% by neurologists and 6.7% by clinicians in other specialties). Slightly more than half (51.4%) of the sample are receiving psychological treatment because of FM. To select our reference population (women between 18 and 70 years of age who meet the London Fibromyalgia Epidemiology Study Screening Questionnaire criteria for fibromyalgia (London-4) ), we first used the associations’ records to select the members who met the two first criteria (*n* = 2,227). We then sent letters to these 2,227 women with information about the study, together with informed consent forms, the London Fibromyalgia Epidemiology Study Screening Questionnaire
[34,35] and other questionnaires covering the remaining variables related to the sample characteristics and participation criteria. As we do not have a second clinical diagnosis confirmation, the London-4 criteria were used to ensure population homogeneity. Although these criteria screen only for widespread musculoskeletal pain and do not take into consideration other clinical aspects of FM, they give an optimal sensitivity (100%) in FM screening population studies and good positive predictive values for women in rheumatology settings
[35].

A total of 972 questionnaires (43.5%) were returned in two runs. The eligibility criteria were then applied, and our selected reference population subsequently consisted of 920 members with FM (44 did not fit the London-4 criteria and 8 questionnaires did not contain enough data). The remaining criteria were that the individual did not walk or the walking pattern did not comply with one or more features of the selected walking program, the individual was without comorbidity which impeded walking or, if there was comorbidity, the individual had received medical advice to walk. A total of 582 members (63.3%) satisfied these criteria. Figure 
1 is a flowchart of the participant recruitment process.

**Figure 1 F1:**
[figure not shown]
**Flowchart of the participant recruitment process.** ADEFA: Fibromyalgia Association of Alicante; AFEFE: Fibromyalgia Association of Elche; AFIBROM: Fibromyalgia Association of Madrid; AFIBROTAR: Fibromyalgia Association of Talavera de la Reina (Toledo); London-4: London Fibromyalgia Epidemiology Study Screening Questionnaire criteria for fibromyalgia.

#### Sample size calculation

We calculated the sample size for the experimental study by taking into consideration the 582 FM participants previously identified as the eligible population derived from the different associations: ADEFA (*n* = 33, 5.7%), AFEFE (*n* = 125, 21.5%), AFIBROM (*n* = 314, 54.0%) and AFIBROTAR (*n* = 110, 18.9%). The expected differential increase in the selected exercise prevalence from baseline is 10% for CG, 20% for IG and 40% for MIG. Given the rule that the frequency of dropouts should not exceed the frequency of the effect, we expect a maximum dropout rate of 30% before random allocation. This percentage will be added to the calculated sample size. We have defined the risk α as 5% and the study power as 80%. The minimum magnitude of the expected effect (in relation to the effect on CG) is 10% for IG and 30% for MIG. After we apply these conditions and dividing the sample population into three experimental groups, each group will consist of 115 persons, which is equal to 345 participants. In previously reported supervised programs of moderate-intensity walking, adherence has ranged from 62%
[14] to only 37.5%
[32]. In other studies, the percentage of patients who finished the supervised program was greater than 70% to 80%
[7,15,36-39]. In other words, studies have shown that more than 20% to 60% of patients do not complete physical activity programs which include walking. Therefore, we added a 30% dropout rate as a reasonable calculation, which gives us a sample size of 449 women with FM.

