#### Randomization

We used a computer program to randomize the three experimental groups and four fibromyalgia associations, taking into account the size of each center
[40]. The 449 participants were allocated to the three experimental groups as follows: CG = 154, IG = 153 and MIG = 142 (Table 
1). We applied another computer program to generate random sequences to select the participants from each fibromyalgia association for the experimental and control groups
[41]. The randomization results will be checked by analyzing potential confounders such as walking patterns, physical activity, impact of FM, pain, emotional status and age (see the “Statistical analysis” subsection below).

**Table 1 T1:** **Randomized experimental group-center assignments**^
**a**
^

**Patient associations**	**Assignment, **** *n * ****(%)**			**Total**
	**CG**	**IG**	**MIG**	
ADEFA	7 (28.0)	9 (36.0)	9 (36.0)	25 (100)
AFEFE	42 (39.6)	29 (27.4)	35 (33.0)	106 (100)
AFIBROM	73 (33.2)	87 (39.5)	60 (27.3)	220 (100)
AFIBROTAR	32 (32.7)	28 (28.6)	38 (38.8)	98 (100)
Total	154 (34.3)	153 (34.1)	142 (31.8)	449 (100)

^a^ADEFA: Fibromyalgia Association of Alicante; AFEFE: Fibromyalgia Association of Elche; AFIBROM: Fibromyalgia Association of Madrid; AFIBROTAR: Fibromyalgia Association of Talavera de la Reina (Toledo); CG: Control group; IG: Implementation intention group; MIG: Motivation and implementation intention group.

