#### Phase II (second and third years)

As our main outcome is a binary variable, backward stepwise logistic regression analysis will be applied. This method will allow us to investigate whether the experimental condition is associated with the acquisition of the walking pattern. Analysis will be performed for each time measure. Changes in walking behavior over time will be analyzed by applying a Cox proportional hazards regression model for recurrent events. Using this methodology, we will estimate the hazard function of the outcome measure (the likelihood of walking over time). We will analyze differences between groups by introducing the experimental condition as a predictor of the moment in the longitudinal study when women maintained the walking pattern.

Randomization results will be checked to ensure that groups are comparable at the beginning of the study in terms of their distribution of potential confounding factors (walking pattern, IPAQ, FIQ, pain, age, emotional status and behavioral intention). The potential confounders will be selected according to previous analyses at baseline by applying confusion criteria (associations with exposition: *P* ≤ 0.20 and correlation coefficients >0.10; associations with the main result in CG: OR < 0.67 or OR > 1.5). Statistical adjustment to control for the impact of confounders on effect estimation will be applied by introducing them into the analyses (if changes in OR are greater than 10%). Effect modifiers of basal walking pattern will also be tested.

Multiple regression analysis will be performed for each secondary outcome variable. Baseline data will be introduced in the predictive model for each time measure. We will test the mediating effects of the behavioral intention and of implementation intentions in the total sample using path analysis.

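### At 115 women per group, the stated 80% power is not met for the stated 10-point minimum effect of IG over CG: it is about 57% two-sided, or 69% one-sided

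*Protocol article*

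**What the plan says.** All the inputs stand in one paragraph of the protocol article, under Sample size calculation.

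- Expected rates: "The expected differential increase in the selected exercise prevalence from baseline is 10% for CG, 20% for IG and 40% for MIG".
- Minimum effects against control: "The minimum magnitude of the expected effect (in relation to the effect on CG) is 10% for IG and 30% for MIG".
- Error rates, in per cent: "We have defined the risk α as 5% and the study power as 80".
- Result: "each group will consist of 115 persons, which is equal to 345 participants".
- Dropout is added afterwards: "Therefore, we added a 30% dropout rate as a reasonable calculation, which gives us a sample size of 449 women with FM". The 115 is therefore the number per group net of dropout.

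The section names no formula, sidedness, continuity correction or multiplicity adjustment. The main outcome is binary (Statistical analysis, Phase II: "As our main outcome is a binary variable, backward stepwise logistic regression analysis will be applied"), so comparing two proportions is the natural check.

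Three other places bear on the point:

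- **Main hypothesis** (Description of the overall project): it concerns MIG against CG and MIG against IG.
- **Primary outcome measures:** expected efficacy of MIG is given as 30% above CG and 10% above IG.
- **Statistical analysis, Phase I:** all 582 eligible women were contacted, and 274 accepted and attended the first evaluation session.

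**The concern.** A single, unqualified 80% is attached to a set of conditions that includes a 10-point effect of IG over CG. A reader will take it that 115 per group is enough to detect that effect. Ten points on a control rate of 10% is much the hardest of the effects listed in that section, and 115 looks too small for it.

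IG against CG is the only contrast that sets implementation intentions alone against the control condition. If the planned effect is real and power is about 57%, a two-sided test misses it about 43% of the time. Anyone relying on the stated 80% would give a non-significant result on this contrast more weight than it deserves.

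**Working it through.** **Inputs.** Alpha 5%, power 80%, rates 10% (CG), 20% (IG) and 40% (MIG), and n = 115 per group, all from Sample size calculation. The rates are increases from baseline. Eligible women were those for whom "the individual did not walk or the walking pattern did not comply with one or more features of the selected walking program", so baseline compliance is taken as about zero and the increases are read as endpoint rates. Sidedness is not stated, so both are shown.

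**Formula** (two proportions, pooled variance under the null). With d = p2 − p1, p̄ = (p1 + p2)/2, S0 = √[2p̄(1 − p̄)] and S1 = √[p1(1 − p1) + p2(1 − p2)]:

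- n per group = [(z_α·S0 + z_β·S1)/d]²
- power = Φ[(d√n − z_α·S0)/S1]

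**Trying to reproduce 115.** For 10% against 20%: p̄ = 0.15, S0 = √0.255 = 0.505, S1 = √0.25 = 0.5.

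- Two-sided: n = [(1.960 × 0.505 + 0.842 × 0.5)/0.10]² = 198.96, so 199 (219 with continuity correction).
- One-sided: n = [(1.645 × 0.505 + 0.842 × 0.5)/0.10]² = 156.6, so 157.
- The other contrasts, two-sided, need 82 (20% against 40%) and 32 (10% against 40%).

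None of these is 115. The formula returns 115 for 10% against 20% at one-sided alpha 0.10, which is not the stated 5%. A finite-population correction for the 582 eligible women, applied to the two-arm total, comes close: 398/(1 + 397/582) = 236.6, or 118 per group. The section states no such correction, and it would not be valid for the power of a randomised comparison.

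**Power at 115 per group, IG against CG.** d√n = 0.10 × √115 = 1.072.

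- Two-sided: (1.072 − 0.990)/0.5 = 0.165; Φ = 56.6%. Exact enumeration of the same test gives 57.1%.
- One-sided: (1.072 − 0.831)/0.5 = 0.483; Φ = 68.6%.

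**All contrasts at 115 per group**

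| Contrast | Rates | Two-sided | One-sided |
|---|---|---|---|
| IG vs CG | 20% vs 10% | 57% | 69% |
| MIG vs CG | 40% vs 10% | >99% | >99% |
| MIG vs IG, as in Sample size calculation | 40% vs 20% | 92% | 96% |
| MIG vs IG, if 10 points as in Primary outcome measures | 40% vs 30% | 35.5% | 48% |

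For the last row, two-sided: p̄ = 0.35, S0 = 0.6745, S1 = 0.6708; (1.072 − 1.322)/0.6708 = −0.372; Φ = 35.5%. Reaching 80% would need 356 per group.

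**Sensitivity of IG against CG (two-sided).**

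- A 10-point gap on a higher control rate has less power: 42% for 30% against 20%.
- On a lower control rate it has more: 72% for 15% against 5%, and 85% for 12% against 2%. Only a control rate far below the stated 10% reaches 80%.
- The smallest rise over 10% detectable with 80% power at 115 per group is about 13.8 points.

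**At the reported attendance.** 274/3 ≈ 91 per group. Two-sided: 0.10 × √91 = 0.954; (0.954 − 0.990)/0.5 = −0.072; Φ = 47%.

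**The case against.** **IG against CG is not in the main hypothesis.** This is true, and it limits the consequence. The hypothesis sets MIG against CG and against IG, and the primary outcome section gives expectations for those two contrasts only. But the sample size section itself lists the 10-point IG effect among the conditions it applies under one 80% claim, so that claim is still wrong for that effect.

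**The hypothesis is directional, so a one-sided test may be meant.** The protocol does not say so. Even then, power is 69%.

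**More women were allocated than 115 per group:** "The 449 participants were allocated to the three experimental groups as follows: CG = 154, IG = 153 and MIG = 142". With no loss at all, 154 against 153 gives 69% two-sided and 79% one-sided. That ignores the 30% dropout the plan itself allows for.

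**The primary outcome section may imply a larger IG effect.** If MIG is 40% and only 10 points above IG, then IG is 30%, 20 points above CG. Power for IG against CG would then be Φ[(0.20√115 − 1.960 × √0.32)/√0.30] = Φ(1.89) ≈ 97%. This stands as a reason to reconcile the two sections. It does not rescue the 80%: with CG at 10% and MIG at 40%, one of the two contrasts involving IG is then only 10 points wide and underpowered at 115, whichever section holds.

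**Stronger readings that do not hold.** A reader might infer that the whole trial is underpowered. MIG against CG is not, on any figure given. A reader might instead infer that both MIG contrasts are safe and that the trial can be called sized for them. The 92% for MIG against IG rests on one of two conflicting statements, so this is not established. Nor does the protocol say that a null IG–CG result will be taken as proof that planning alone does not work; that is a risk of misreading and not a stated intention.

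**Conclusion.** The stated 80% power at alpha 5% does not hold for the stated 10-point minimum effect of IG over CG. At 115 analysable women per group, power is about 57% two-sided or 69% one-sided, a shortfall of 23 or 11 points. The number needed is 199 or 157 per group.

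This rests on endpoint rates of 10% and 20%, baseline compliance near zero, and no multiplicity adjustment. An adjustment would lower the figure further: 45% at two-sided alpha 0.025.

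MIG against CG is amply powered. MIG against IG stays open, between about 35.5% and 92% two-sided, until the two sections agree.

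These are design-stage figures and should not be read as the power the trial will have. The 274 women at the first evaluation make about 91 per group before further loss, which gives about 47% two-sided for IG against CG. The Discussion plans to contact 180 more women, so the final number is not settled.

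**What to change.** In Sample size calculation, replace the single 80% with power by contrast. Label the figures as design-stage at 115 per group, and give sidedness, formula and assumed rates.

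- **MIG against CG** (40% against 10%): above 99%.
- **IG against CG** (20% against 10%): 57% two-sided (69% one-sided). Report it as an estimate with a confidence interval, with no claim of 80% power.
- **MIG against IG:** first reconcile the 20-point gap implied in Sample size calculation with the 10% in Primary outcome measures. State the power that follows, and do not say that the trial is sized for this contrast until that is done. If the reconciliation changes the assumed IG rate, recompute the IG–CG figure too.

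Add one sentence saying that the figures assume 115 per group, and that at 274 women (about 91 per group before further loss) IG against CG has about 47% power two-sided.

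The cost is a few sentences and one less favourable stated figure. No extra participants are needed, and the design does not change.

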#### Primary outcome measures

Two primary outcomes will be assessed as indicators of each intervention’s effect on exercise adherence:

1. We will measure the proportion of participants who perform the full minimum walking criteria (at least 30 minutes in bouts of 15 minutes with a small rest between bouts, twice times weekly over a minimum of 6 consecutive weeks) at the end of the 6-week period and the proportion of participants who have maintained it at 3 and 9 months. The expected efficacy of MIG is 30% higher than CG and 10% higher than IG.

2. Among participants who perform the full minimum walking criteria, we will focus on the proportion who reach the recommended pattern for FM patients at week 6 (between two and four times weekly for about 50 minutes in bouts of 15 to 20 minutes over a minimum of 6 consecutive weeks)
[31].

We will use the same self-reported measurements of the behavior from phase I (*ad hoc* self-reported items and daily logs) and pedometer readings.

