All eligible individuals were contacted (*N* = 582) because of the difficulties involved in the participation of the first 449 selected women, such as the failure to contact them after repeated attempts, nonattendance after three citations and distance of residence from the study location. Ultimately, 274 patients accepted and attended the first evaluation session (participation rate = 47.1%). No significant differences were found between these 274 participants and women with FM who did not participate in this phase of the study (*n* = 308) on the basis of any of the above-mentioned variables (age: *t* = 0.767, *P* = 0.443, df = 579; education level: χ^2^ = 5.567, *P* = 0.135; df = 3; employment status: χ^2^ = 7.567, *P* = 0.272, df = 6; pain intensity perception: *t* = 0.389, *P* = 0.697, df = 579; fatigue: *t* = -0.178; *P* = 0.858, df = 576; fatigue upon waking: *t* = 0.785, *P* = 0.433, df = 576; impact perception of fatigue: *t* = 0.410, *P* = 0.410, df = 577; cognitive problems: *t* = -0.718, *P* = 0.473, df = 577; impact perception of cognitive problems: *t* = -0.939, *P* = 0.348, df = 577; impact perception of sleeping disorders: *t* = -0.107, *P* = 0.915, df = 577). The groups showed different medians of moderate activities (*P* ≤ 0.01), but similar medians in total activity (*P* = 0.066), sitting (*P* = 0.208), walking (*P* = 0.609) and vigorous activities (*P* = 0.115). In addition, the groups presented a proportion of noncompliance similar to that of the total unsupervised pattern (45.8% and 44.2%, respectively) and the same proportion reported for medical recommendation to walk (81.8% in each group) (Table 
5).

Internal consistency analysis will be performed for the different scales using the Cronbach’s α coefficient. Path analysis will be conducted to identify the relative weights of attitudes, perceived norms and perceived behavioral control in the prediction of the behavioral intention (path coefficients). Furthermore, we will test the role of the fear of movement, pain and FM impact. Spearman and Pearson correlations and cross-tabulation analysis (depending on the variables) will be used to explore the agreement of the behavioral measurements.

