It is important to underline that as soon as the final 274 participants agree to participate, strategies to avoid having participants dropping out will be implemented. In that sense, we will contact the 180 women who failed to attend the evaluation session but did not refuse to participate in the study. Because the participants belong to FM associations which conduct other activities for their members, we may have problems with the masking process. Participants might talk among themselves about the activities performed in each intervention group. However, nobody knows which intervention group is expected to be more successful. Participants will sign a commitment of confidentiality, and, furthermore, we will also assess the shaping of implementation intentions in the control group.

In spite of these limitations, the study addresses an important need: the enhancement of self-management in the treatment of FM. It focuses on increasing adherence to a strategy which has been shown to be effective (physical exercise, specifically walking). Furthermore, the results are expected to show the effectiveness of a short intervention which is easily applicable with a minimum of training and cost and that can be incorporated into routine clinical practice.

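### The 30% dropout allowance is multiplied on (449) instead of divided out (493), and size and power are not restated for the 274 women who attended

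*Protocol article*

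**What the plan says.** Protocol article, Sample size calculation: with α at 5% and power at 80%, each of the three groups needs 115 women, 345 in total. The rates behind this are: "The expected differential increase in the selected exercise prevalence from baseline is 10% for CG, 20% for IG and 40% for MIG". The effects against control are: "The minimum magnitude of the expected effect (in relation to the effect on CG) is 10% for IG and 30% for MIG".

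On dropout, the same section first says "we expect a maximum dropout rate of 30% before random allocation". It then cites studies in which patients did not finish walking or exercise programmes, and concludes: "Therefore, we added a 30% dropout rate as a reasonable calculation, which gives us a sample size of 449 women with FM". The Randomization section reports that all 449 were allocated (CG 154, IG 153, MIG 142).

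The Phase I part of the Statistical analysis says that all 582 eligible women were contacted because of difficulties with the first 449, and then: "Ultimately, 274 patients accepted and attended the first evaluation session". The Discussion uses the phrase "as soon as the final 274 participants agree to participate" and adds that 180 women who missed the session without refusing will be contacted.

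Primary outcome measures restates the effects: "The expected efficacy of MIG is 30% higher than CG and 10% higher than IG".

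**The concern.** There are three linked problems.

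- **Inflation.** A dropout rate is a fraction of those who start. Adding 30% of the target to the target does not protect it against losing 30% of a larger starting number.
- **Timing.** The 30% is defined as loss before allocation but justified by failure to complete programmes, which happens after women have started. The Randomization section then allocates the full 449. A reader cannot tell which loss the allowance covers, or whether anything is set aside for loss over the 9 months of follow-up.
- **Attendance.** The article sets a target of 345 and reports 274 without connecting the two.

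The main hypothesis (Description of the overall project) requires MIG to beat control and to do better than the volitional intervention alone. A null MIG v IG result can be interpreted only if the power for that contrast is known at the number of women who actually enter.

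**Working it through.** **1. Reproduce the stated size.** Inputs from Sample size calculation: 3 × 115 = 345, dropout 30%.
345 × (1 + 0.30) = 448.5, rounded up to 449. This matches.

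**2. Size that keeps 345 after 30% loss.**
345/(1 − 0.30) = 492.9, so 493 (495 if rounded to 165 per group). This is 44 more than 449 and within the 582 eligible.

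**3. What 449 protects.**
449 × 0.70 = 314.3, about 105 per group and 31 short of 345.
Largest loss that still leaves 345: 1 − 345/449 = 23.2%.

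**4. Attendance.**
345 − 274 = 71 short; 274/3 = 91.3 per group.
All 180 re-contacted women join: 274 + 180 = 454; 454 × 0.70 = 317.8, about 318.
Reaching 493 from 274 needs 219 more women, which exceeds 180.
Scenario of a further 30% loss from 274: 274 × 0.70 = 191.8, about 64 per group.

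**5. Power per contrast.** Assumptions: 10%, 20% and 40% are end rates (the article calls them increases from baseline, so this takes baseline prevalence as about zero); two-sided 5%, no multiplicity adjustment; equal groups; no continuity correction. With p̄ the mean of the two rates:

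power = Φ{ [ |p1 − p2|√n − 1.96√(2p̄(1 − p̄)) ] / √(p1(1 − p1) + p2(1 − p2)) }

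For MIG v IG at n = 91.3: (0.20 × 9.555 − 1.96 × 0.648)/0.632 = 1.01, giving 84%.

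| Per group | Origin | MIG v CG (40 v 10) | MIG v IG (40 v 20) | IG v CG (20 v 10) |
|---|---|---|---|---|
| 115 | stated target | >99.9% | 92% | 57% |
| 105 | 449 less 30% | 99.9% | 89% | 53% |
| 91 | 274/3 | 99.8% | 84% | 47% |
| 64 | 274 less 30% (scenario) | 98% | 70% | 35% |

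**6. Sensitivity of MIG v IG.** At α = 0.05/3 the four rows become 83%, 78%, 71% and 53%. The Sample size section implies a gap of 30 − 10 = 20 points, while Primary outcome measures gives 10%. At 40% v 30% and unadjusted 5%, power is about 35% at 115 per group and 29% at 91.

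**7. Base calculation.** By the same method, 80% power needs 32 per group (40 v 10), 82 (40 v 20) and 199 (20 v 10). The stated 115 matches none of these.

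**The case against.** The inflation step is disclosed and its effect is small. On the 40% v 20% rates, a full 30% loss from 449 moves MIG v IG power from 92% at 115 per group to 89% at 105. Changing 449 to 493 would not have altered recruitment either, because every eligible woman was contacted. Reporting the planned size alongside actual attendance is also ordinary in a protocol article. And 274 is attendance at a first evaluation session, with 180 women still to be approached, so it may not be the trial's final number.

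Much of this stands. A reader might infer from 449 and 274 that the 80% power is lost; the documents do not support that. On the stated rates neither the inflation step nor the 274 attendance takes either MIG contrast below 80% at an unadjusted 5%. The weak IG v CG figures are not evidence for that inference either: that contrast has 57% power at the full 115, so its shortfall comes from the base calculation. Nor should 64 per group be read as the plan's own forecast. It takes a further 30% off 274, which applies only if the allowance means loss after allocation.

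What the objection does not remove: 449 does not do what the text says it does, the 30% has two incompatible meanings, and 345 stands beside 274 without comment. Full success in re-contacting women would lift the number above 345 at entry, but not after a 30% loss.

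**Conclusion.** The point holds as a wrong sample-size figure with an unrevised size and power statement. The inflated size should be 493; 449 protects 345 only up to about 23% loss.

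The consequence for power differs by contrast. MIG v CG is secure, at 98% or more in every case at the unadjusted 5%. MIG v IG falls below 80% if women are lost after allocation from 274 on the scale of the 30% scenario, if α is divided by three (already 78% at 105 per group), or if the 10-point gap in Primary outcome measures is the intended one. IG v CG is underpowered from the start.

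These figures rest on the end-rate reading of 10/20/40%, a two-sided test and equal groups. The article does not state the sidedness of the test or the contrast to which its 80% applies. The conflict over the MIG-IG gap moves the power for that contrast more than the choice between 449 and 493 does, so it has to be settled before any power for MIG v IG is quoted.

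**What to change.** 1. In Sample size calculation, replace 449 with 345/0.70 = 493, or keep 449 as the number selected and state that it protects 345 only up to about 23% loss.
2. State whether the 30% is loss before or after allocation, and align the definition, the cited justification and the Randomization section with that choice.
3. Reconcile the MIG-IG effect between Sample size calculation (20 points implied) and Primary outcome measures (10%).
4. Add power for each of the three contrasts at the number actually entering: at present 274, about 91 per group. Show the 64-per-group case as a labelled scenario of further loss. State the sidedness, any multiplicity adjustment and the end-rate assumption. Update the figures if re-contacted women join.
5. Say which contrast the 115 per group was computed for, and acknowledge that IG v CG has about 57% power even at that size.

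The cost is text only. Correcting the statement needs no extra recruitment, but the stated figures become less favourable.
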